### Standardised trial medicines

Chinese herbal medicine in the UK involves the use of plant-based herbal medicines. The standardised herbal formulae have been developed through expert consultation and a literature review conducted prior to the trial. Each formula consists of three herbs (see Additional file 4).

These two formulae are comprised of the following herbs:$$ \begin{array}{l}\mathrm{RUTI}\hbox{-} \mathrm{a}:\\ {}\mathrm{B}\mathrm{a}\mathrm{i}\ \mathrm{H}\mathrm{u}\mathrm{a}\ \mathrm{She}\ \mathrm{She}\ \mathrm{C}\mathrm{a}\mathrm{o}\ \left(\mathrm{Herba}\ \mathrm{H}\mathrm{edyotis}\ \mathrm{Diffusa}\right)\ \left(40\%\ \mathrm{o}\mathrm{f}\ \mathrm{the}\ \mathrm{Formulation}\right)\\ {}\mathrm{H}\mathrm{u}\mathrm{a}\mathrm{n}\mathrm{g}\ \mathrm{B}\mathrm{a}\mathrm{i}\ \left(\mathrm{Cortex}\ \mathrm{Phellodendron}\ \mathrm{Amurense}\right)\ \left(20\%\ \mathrm{o}\mathrm{f}\ \mathrm{the}\ \mathrm{Formulation}\right)\\ {}\mathrm{J}\mathrm{i}\mathrm{n}\ \mathrm{Qian}\ \mathrm{C}\mathrm{a}\mathrm{o}\ \left(\mathrm{Hebra}\ \mathrm{Lysimachia}\ \mathrm{C}\mathrm{hristinae}\right)\ \left(40\%\ \mathrm{o}\mathrm{f}\ \mathrm{the}\ \mathrm{Formulation}\right)\end{array} $$$$ \begin{array}{l}\mathrm{RUTI}\hbox{-} \mathrm{p}:\\ {}\mathrm{Huang}\ \mathrm{Qi}\ \left(\mathrm{Radix}\ \mathrm{Astragalus}\ \mathrm{Membranaceus}\right)\ \left(50\%\ \mathrm{o}\mathrm{f}\ \mathrm{the}\ \mathrm{Formulation}\right)\\ {}\mathrm{W}\mathrm{u}\ \mathrm{Y}\mathrm{a}\mathrm{o}\ \left(\mathrm{Radix}\ \mathrm{Lindera}\ \mathrm{Strychnifolia}\right)\ \left(25\%\ \mathrm{o}\mathrm{f}\ \mathrm{the}\ \mathrm{Formulation}\right)\\ {}\mathrm{K}\mathrm{u}\ \mathrm{Shen}\ \left(\mathrm{Radix}\ \mathrm{Sophorae}\ \mathrm{Flavescentis}\right)\ \left(25\%\ \mathrm{o}\mathrm{f}\ \mathrm{the}\ \mathrm{Formulation}\right)\end{array} $$

In terms of modern pharmacology, the herbal formulae are reported to have the following main functions (see Additional file 4):RUTI-a has antibacterial and anti-inflammatory actions.RUTI-p has immune enhancing, anti-inflammatory, antibacterial, and mildly diuretic actions.

These standardised herbs will be administered as 0.4 g capsules (two pills taken twice a day (b.d.) for preventative treatment, and four pills taken four times a day (q.d.) in the event of an acute infection).

### Concealment and emergency unblinding

Concealment will be maintained with packaging in the standardised arm that does not provide any information as to the contents and in the individual arm by the use of identical packaging and by the participant’s herbs not being seen by the CHM practitioner.

Each woman enrolled will be provided with an emergency unblinding card with information on how to access the trial team if required.

Emergency unblinding will be possible by a member of the study team not conducting study assessments, who will use the participant ID number and check allocation by accessing the centralised allocation list stored at the herbal dispensary. Unblinding will be required in case of the following:A compelling medical need as assessed by the treating medical doctor, e.g. a serious adverse event (SAE) has occurred, and the treatment allocation is required to inform subsequent clinical careIngestion of study products by a childIngestion of excessive amounts of study products either by the participant or by an adult not participating in this study.

### Outcomes (see Figs. 1 & 2)

#### Primary outcome measures

The primary outcomes will be the number episodes of recurrent UTIs during the trial period and in the 6 months of follow up and the number of days of symptoms rated moderately bad or worse according to the patient diaries [10]. These will be assessed by symptom diaries, which will indicate the severity of acute and recurrent UTI symptoms (reporting dysuria, haematuria, frequency during day and night, ‘smelly urine’, ‘tummy pain’, generally feeling unwell, and restriction of daily activities). These diaries have been used in this format for acute respiratory and urinary tract infections and have been validated and shown to be sensitive to change [2, 10].

**Fig. 1 Fig1:**
[figure not shown]
RUTI flow diagram

**Fig. 2 Fig2:**
[figure not shown]
SPIRIT: schedule of enrolment, interventions, and assessments

In addition, participants will also be asked to complete an end-of-month diary in which they record the number of days with symptoms, changes in presentation, time lost from work, and how easy it has been to comply with the herbal medicine regime. These diaries will provide information on the rate and severity of acute infection but also on the impact of low-grade, chronic infection on the lives of women. Participants will be asked to complete both an acute and a monthly diary for the 6-month follow-up to the trial to enable the evaluation of any longer-term changes in infection rates.

#### Secondary outcomes include the following:

The use of antibiotics for acute UTIs elicited from symptom diaries and cross-referenced with GP notesThe Credibility/Expectancy questionnaire, which is used to assess participant attitudes on the effectiveness of CHM prior to and on completion of the trial [25]The Morisky Medication Adherence Scale, which is used to assess compliance with the herbal medicines. In addition participants will be asked to return all herbal containers including those that are empty and those with any unused herbal capsules or granules. These will be counted to help assess whether herbal medicines were taken as instructed.At the end of trial, a Global Ratings of Change pro forma will be used to assess participant perceptions of the overall change in the frequency and severity of their urinary symptoms. An 11-point Likert scale will be used to assess these changes and an improvement of two or more points will be considered as a clinically important change [26].Liver (ALT) and renal (serum creatinine) function tests will be conducted at weeks 0, 4 and 16. Blood results will be used to assess safety of the herbal preparations to ensure that no change in kidney or liver functions occurs (each site was given the specific normal reference ranges for their associated NHS laboratory where the blood was processed.)Economic and quality of life assessment using the validated EQ5D outcome measure.An assessment of blinding using the Bang blinding index (CHM practitioner only).Two nested qualitative studies will also be conducted during this trial. On completion of the trial, semi-structured phenomenological interviews will be conducted with purposively sampled women from all four groups to provide an in-depth exploration of their subjective experiences of taking CHM and conventional care during the trial. We will also investigate the enablers and barriers that affected women’s decisions to participate in the trial. A second study will include interviews of GP practice nurses to explore their experiences of delivering CHM in a clinical trial conducted in primary care.

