### Intervention

All women taking part will be able to consult with their GPs and, if necessary, use conventional medicines such as antibiotics for acute infections. Antibiotic use will be recorded as one of the trial outcomes. These can be taken in conjunction with the ‘acute’ herbal treatment.

Participants in the standardised arm will receive ‘acute’ and ‘preventative’ herbal capsules (Size 0, hypromellose capsules) to be used during and between instances of infection. Matching placebo capsules have been prepared containing therapeutically inert sugar beet fibre. In total, 16 weeks of preventative herbal capsules will be allocated to each participant, with an additional 4 weeks of ‘acute’ capsules to be used in the instance of a UTI occurring.

The individualised arm of the trial will follow routine practice of CHM, which involves a practitioner writing an individualised herbal prescription typically comprising between ten and 15 herbs selected from the Chinese herbal material medica. The selection of herbs is contingent upon a full CHM differential diagnosis made after a detailed consultation process. The formula used will also change over time to address the changing clinical presentation of the patient.

After the consultation with the CHM practitioner verum or placebo herbal medicines will be dispensed as concentrated herbal granules to be taken twice a day. Each dose will be separately packaged in a sealed foil sachet. These granules dissolve in hot water for patients to drink as an herbal decoction. The practitioner may allocate preventative treatment with a clearly labelled standby for an acute infection. Women allocated to placebo treatment will receive identically packaged granules derived from therapeutically inert food colourings and flavourings. Once re-constituted, these placebo herbs resemble the colour and the strong taste and smell of the verum formulae.

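### In the standardised arm, ALT and creatinine at weeks 0, 4 and 16 cannot support a statement on transient liver or renal changes with the acute formula, which is taken only during a UTI

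*Protocol article*

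**What the plan says.** The article fixes both the timing of the blood tests and their purpose (Secondary outcomes): "Liver (ALT) and renal (serum creatinine) function tests will be conducted at weeks 0, 4 and 16". The next sentence gives the use: "Blood results will be used to assess safety of the herbal preparations to ensure that no change in kidney or liver functions occurs". The Discussion counts safety data among what the trial will deliver.

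The standardised arm uses two products, RUTI-a (acute) and RUTI-p (preventative). Under Standardised trial medicines, "Each formula consists of three herbs", and the two lists have no herb in common. The preventative product is taken throughout the 16 weeks. The acute product is supplied under Intervention "with an additional 4 weeks of ‘acute’ capsules to be used in the instance of a UTI occurring". No passage ties a blood draw to an acute course or mentions acute exposure when results are read.

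In the individualised arm, Intervention says: "The formula used will also change over time to address the changing clinical presentation of the patient".

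**The concern.** A fixed draw is informative about a product that the woman is taking, or has recently taken, when blood is drawn. At weeks 4 and 16 that holds for RUTI-p. For RUTI-a it holds only if an infection happens to fall just before one of two dates. Some women will never have taken it, and others will have stopped weeks earlier.

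The stated purpose covers the preparations together. A set of normal results could then be read as reassurance about RUTI-a when few of them followed recent exposure to it. This matters because a larger trial is meant to build on the safety data from this one.

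**Working it through.** The article gives no figure of its own on this point, so there is none to reproduce. The check asks how much RUTI-a exposure the fixed draws would sample.

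**Inputs from the article**
- On-treatment draws at weeks 4 and 16, taken as days 28 and 112 (Secondary outcomes).
- Treatment period of 16 weeks, or 112 days (Abstract).
- Forty women in the standardised arm with equal allocation to active and placebo, so about 20 on active capsules (Methods/design).
- At least three UTIs in the previous 12 months (Inclusion/exclusion criteria).

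**Assumptions, because the article gives no values**
- The entry rate of 3 a year continues on treatment, with Poisson counts, and every episode is treated with RUTI-a.
- Course length L is 7 days (range tried: 3 to 14).
- Onset is uniform over days 0 to 112.
- A change remains detectable for W days after the course ends (range tried: 0 to 28).

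**Step 1: women never exposed.** Expected episodes per woman = 3 × 16/52 = 0.92. P(no episode) = exp(−0.92) = 0.40. Among 20 women, about 8 never take RUTI-a. At 6 UTIs a year, 20 × exp(−1.85) gives about 3. At 2 a year, which is below the entry minimum and would apply only if the rate fell on treatment, 20 × exp(−0.62) gives about 11.

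**Step 2: courses sampled.** Share with a draw during the course or within W days after it = [min(L+W, 28) + min(L+W, 84)]/112.

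| L (days) | W (days) | Share sampled |
|---|---|---|
| 7 | 0 | (7+7)/112 = 12.5% |
| 7 | 7 | (14+14)/112 = 25% |
| 7 | 14 | (21+21)/112 = 37.5% |
| 7 | 28 | (28+35)/112 = 56% |
| 3 | 0 | (3+3)/112 = 5% |
| 14 | 28 | (28+42)/112 = 62.5% |

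A simulation of one million onsets agreed for the four 7-day rows. Over all combinations tried, between 37.5% and 95% of courses have no draw in their window.

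**Step 3: what a clean result would mean.** Expected courses among the active women = 20 × 0.923 = 18.5. With 7-day courses, about 18.5 × 0.125 = 2.3 have a draw during the course, and about 18.5 × 0.375 = 6.9 during it or within 14 days after. With no abnormal result in n sampled courses, treated as independent, the one-sided upper 95% limit is 1 − 0.05^(1/n):
- n = 2: 78%
- n = 7: 35%
- n = 20, if all active women were counted as informative about RUTI-a: 14%

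**Step 4: illustration.** Suppose 10% of courses caused a transient change. If every course were sampled in its window, the chance of seeing no abnormal result would be 0.90^18.5 = 0.14. With 37.5% sampled it is (1 − 0.10 × 0.375)^18.5 = 0.49. With 12.5% sampled it is (1 − 0.10 × 0.125)^18.5 = 0.79. The 10% is for illustration only.

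**The case against.** The strongest reply is that the article never says results will be pooled across formulae, that acute exposure will be ignored, or that RUTI-a will be declared safe. This is right. A reader might infer that the plan will credit normal results to RUTI-a and so falsely clear it, but the text does not say so. What stands is narrower: the stated use covers all the preparations, and for the as-needed one the fixed draws cannot bear that inference on transient changes.

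A second reply is that table layout belongs in the analysis plan, and that the full protocol or the schedule figure, neither of which is shown, may provide for unscheduled tests. For layout alone this would settle the matter. Here, though, the article itself fixes both the timing and the purpose, and the two do not fit for RUTI-a.

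Third, safety does not rest on these tests alone. Adverse effects are described, and an independent committee including a toxicologist reviews abnormal bloods and adverse events. This also stands, so it would be wrong to infer that the acute formula goes unmonitored. These safeguards would not, however, reveal a symptomless change that was never sampled. A lasting change would still appear at week 4 or 16.

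Fourth, about 20 active women cannot clear any formula, however the table is arranged. That is true, and it is a further reason to report the number actually sampled.

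Finally, a reader might build the point on dose. By capsule mass the acute regimen is 4 × 4 × 0.4 g = 6.4 g a day, against 2 × 2 × 0.4 g = 1.6 g for prevention. That fourfold ratio compares two different formulae in one arm only. It also rests on "four pills taken four times a day (q.d.) in the event of an acute infection", where the abbreviation can be read as once daily, which would give 1.6 g and a ratio of 1. The point does not need the ratio.

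**Conclusion.** The point holds for the standardised arm and for transient laboratory changes. About 8 of 20 active women would contribute no information on RUTI-a (about 3 at 6 UTIs a year). With 7-day courses, about 1 course in 8 would have a draw during it, and about 3 in 8 during it or within 14 days after. These sizes depend on the assumed UTI rate, course length and persistence of a change. The direction does not, as long as RUTI-a is taken only during infections and the draws are fixed.

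The documents do not support three stronger readings: that the plan will declare RUTI-a safe, that safety is otherwise unmonitored, or that the problem comes from a fourfold dose. In the individualised arm the changing prescription is itself the intervention, so results there can be read only as referring to individualised prescribing as a whole.

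**What to change.** Leave the blood-test schedule as it is and change the reporting.

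1. In the standardised arm, report ALT and creatinine at each draw by whether an acute course occurred beforehand and by the time since it.
2. Use acute-diary episode dates and returned-capsule counts as a proxy for exposure. The article does not say that dates of acute-capsule use are recorded. If they are not, add a diary item for start and stop dates.
3. Give the data monitoring committee the same table.
4. Limit any laboratory safety statement on RUTI-a to the women sampled during or shortly after a course, and state their number.
5. In the individualised arm, state that results refer to individualised prescribing as a whole. A breakdown by formula would give mostly rows of one woman.
6. Separately, reconcile the wording and the abbreviation of the acute dosing frequency under Standardised trial medicines. No view is taken here on which is right.

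The cost is one table, possibly one diary item, and a narrower safety claim for the acute formula.

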### Research ethics and governance

Obtaining regulatory approval from the Research Ethics Committee, the MHRA, and NHS Research and Development has been an important outcome for this trial. Initial submissions were made to the MHRA in October 2014, and final approval was granted in November 2015. Requests for ethical approval were made in August 2014 and multi-centre approval was granted by the London Surrey Borders Research Ethics Committee in December 2015. (Ref: 14/LO/1425 and by the MHRA (EudraCT number: 2013-004657-24). The lead research and development organisation was the Wessex Clinical Research Network. A more detailed account of the unique challenges required to gain these approvals has been provided in the discussion section. In addition the following ethical issues required clarification:

All women participating in the trial will be able to continue their pattern of usual care alongside taking CHM (see Additional files 2 and 3). Antibiotics can be accessed from their GPs as a rescue package in the event of a serious UTI occurring.

All herbs to be used in the individualised arm of the trial are currently in daily usage within the UK under Regulation 3 of The Human Medicines Regulations 2012 (formally Section 12(1) of the Medicines Act 1968), which permits unlicensed herbal remedies to be made up and supplied by a practitioner to meet the needs of an individual patient following a one-to-one consultation. Regulation 3 remedies are not subject to a regime of specific safety or quality requirements and currently there are no restrictions in terms of those who operate under this regime.

### Data management

#### Confidentiality

All point-of-care test specimens, evaluation forms, reports and other records will be identified in a manner to maintain participant confidentiality and in accordance with the Data Protection Act 1998. All records will be kept in a secure storage area on site with access restricted only to staff delegated duties on the study. Clinical information will not be released without the written permission of the participant, except in cases of emergency or as necessary for monitoring and auditing by the study sponsor. All study staff must comply with the Data Protection Act 1998 and abide by the requirements of the University of Southampton relating to the collection, storage, processing and disclosure of personal information. Any data from this research will be stored according to the University of Southampton Data Protection policy. Written and digitally recorded data will be stored on a password protected computer that will be kept in a secure environment. Any papers connected with this trial will be kept in secure University storage for 10 years and will only be viewed by the research team.

### Data monitoring committee

An independent data monitoring committee has been established to review the results of any abnormal blood tests, adverse events, and other relevant data to decide whether or not the trial should continue. The committee will comprise of a medical statistician, a consultant urologist and a medical Toxicologist.

### Data analysis

The primary outcomes from this study are descriptive, relating to the feasibility of recruitment, the acceptability of randomisation, study medications and outcome measures including patient diaries, and the retention of randomised patients in the study. We will also describe additional data on adverse effects, antibiotic use and adherence to medication, beliefs and expectations of participants, health economics and changes in quality of life.

Although the trial is not powered to provide estimates of effect, exploratory analysis will be undertaken to estimate any effect of individualised, standardised and placebo treatments on the primary outcomes of reducing the frequency and severity of recurrent UTIs.

Continuous outcomes will be explored using linear regression, provided the assumptions underlying the model are met. If not, non-parametric methods will be used. Binary measures will be analysed using logistic regression and count models using an appropriate count distribution. All analyses will be on an intention-to-treat basis and will control for important confounders. Results will be reported in accordance with CONSORT guidelines.

We will analyse any missing data to see if any recurrent patterns emerge, and we will record the numbers and reasons given for participant withdrawal or loss to follow-up, as these are key feasibility outcomes that will inform a larger trial.

Data from the trial will be entered into SPSS 22 for Windows (SPSS Inc., Chicago) and the analysis completed using Stata 14 (StataCorp).

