**Methods/design:**

The RUTI trial is a double-blind, randomised, placebo-controlled, feasibility trial. A total of 80 women will be randomised to ‘individualised’ herbs prescribed by a Chinese herbal practitioner or to ‘standardised’ herbs provided by primary care clinicians. Both arms will have herbs for prevention of UTIs and treatment of acute episodes. Treatment duration is for 16 weeks.

The primary outcomes are the number of episodes of recurrent UTIs during the trial period and in the 6 months of follow-up, and the number of days of symptoms rated moderately bad or worse based on patient diaries. Secondary outcomes will assess participant expectations and beliefs, adherence to the treatment, adverse events and health economics and provide quantitative and qualitative assessments of the impact of recurrent infections on the lives of women.

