## Methods/design

The trial has two separate but linked arms (see Additional file 1). Forty women from the Wessex, South and Northwest London and the Brighton and Hove areas of the Clinical Research Network (CRN) will be randomised to take traditional individualised herbal prescriptions following consultation with a registered CHM practitioner at a private clinic. Forty women from Wessex will be randomised to standardised ‘prescriptions’ of herbal capsules administered via nurses and doctors from GP practices. Both arms will have equal allocation to active and placebo medications. The trial is fully blinded with only the herbal dispensaries knowing the treatment allocation of the women.

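### Logistic regression with confounder control is set for binary measures with no small-sample alternative, at about 20 women per group; only secondary exploratory measures are affected

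*Protocol article*

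**What the plan says.** All references are to the protocol article.

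- **Size.** The Abstract says "A total of 80 women will be randomised". Methods/design splits them into an individualised arm ("Forty women from the Wessex, South and Northwest London and the Brighton and Hove areas") and a standardised arm ("Forty women from Wessex will be randomised to standardised"), and adds "Both arms will have equal allocation to active and placebo medications". The secondary outcomes section also speaks of "purposively sampled women from all four groups".
- **Method.** Data analysis states "Binary measures will be analysed using logistic regression", and then "All analyses will be on an intention-to-treat basis and will control for important confounders". In the same paragraph, linear regression has a non-parametric fallback if its assumptions fail, and counts are left to a suitable distribution. Binary measures have one method and no alternative.
- **Status.** Data analysis calls the effect analysis exploratory and says the trial is not powered for it. The clinical primary outcomes (Primary outcome measures) are numbers of episodes and of symptom days.
- **A possible binary measure.** For the Global Ratings of Change, "an improvement of two or more points will be considered as a clinically important change".

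**The concern.** Maximum-likelihood logistic regression has two known weaknesses in small samples. If one group has no events, or only events, the treatment odds ratio has no finite estimate. If a finite estimate exists and there is a true effect, the log odds ratio is biased away from zero, and more so with each covariate added. The plan requires covariates in all analyses and has about 20 women per group, so both weaknesses are in play.

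At stake is the usefulness of any modelled binary result. Research objectives asks for a provisional effect size to inform a later trial. An infinite or inflated odds ratio serves that aim poorly, and calling the analysis exploratory does not remove the bias.

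**Working it through.** **Group size.** 80 women / 2 arms / 2 treatments = 20 per group before dropout. The article gives no power or precision calculation, so there is no stated figure to reproduce.

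**Assumptions.** Event rates and the number of confounders are not given. Uncommon outcomes are taken at 5–20% and common ones at 70% v 40%, with zero to five covariates. The article does not say whether the two placebo groups are pooled, so both cases are shown.

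**Step 1: empty cells, no covariates.** For a group of n with risk p, the chance of all or no events is f = (1 − p)^n + p^n. The chance that at least one of two groups is affected is 1 − (1 − f1)(1 − f2). At p = 5%, f is 0.95^20 = 0.358 for n = 20 and 0.95^40 = 0.129 for n = 40. Hence:

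- 20 v 20: 1 − (1 − 0.358)² = 0.59
- 20 v 40: 1 − (1 − 0.358)(1 − 0.129) = 0.44

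| Risk in both groups | 20 v 20 | 20 v 40 (placebo pooled) |
|---|---|---|
| 5% | 59% | 44% |
| 10% | 23% | 13% |
| 15% | 8% | 4% |
| 20% | 2% | 1% |

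If one of two groups of 20 has half the stated risk, the chance is 75% at 5% and 44% at 10%. If all active women were compared with all placebo women (40 v 40), it is 24% and 3%.

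**Step 2: uncommon outcomes with covariates.** Covariates cannot rescue an empty cell. In simulation (20 v 20, true odds ratio 0.5, two to five covariates), the treatment coefficient was not finite in 63–72% of trials at a control risk of 5%, and in 33–41% at 10%. Some coefficient in the model was not finite in 84–87% and 58–63%. These figures should not be compared directly with Step 1, because the simulated covariates raise the average risk slightly.

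**Step 3: common outcomes.** The true log odds ratio is ln[(0.4/0.6)/(0.7/0.3)] = ln(0.286) = −1.25. Trials were simulated with independent normal covariates, each with a log odds ratio of 0.4, and fitted by maximum likelihood. A finite estimate almost always existed.

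| Covariates | Overstatement of log OR, 20 v 20 |
|---|---|
| 0 | about 7% |
| 2 | about 16% (mean −1.45) |
| 4 | about 24–29% (for example, mean −1.61) |

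On the odds ratio scale, exp(−1.25) = 0.29 becomes exp(−1.45) = 0.23 with two covariates and exp(−1.61) = 0.20 with four. In one 80-woman model (placebo 40, active 20 + 20), the overstatement is about 5–14% over the same range of covariates.

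**Step 4: bias against sampling error.** In 20 v 20 with four covariates, the bias is 0.24 to 0.29 × 1.25 = 0.30 to 0.36. The standard error of the log odds ratio for common outcomes in 20 v 20 is 0.68–0.89. In the 80-woman model with four covariates, the bias is at most 0.14 × 1.25 = 0.18, against a standard error of about 0.66.

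**Step 5: does the alternative work?** Firth's penalised likelihood on common outcomes was always finite, with a mean log odds ratio 0.95–1.05 times the truth at 20 per group. Maximum likelihood gave 1.07–1.38 times the truth. For 5–10% outcomes, Firth fails only if no event occurs at all, but it remains very imprecise. A risk difference can be given even with an empty cell. As an illustration, take 0/20 v 2/20. The Wilson limits are 0 to 0.161 and 0.028 to 0.301. Newcombe's interval for the difference of 0.10 runs from 0.10 − √(0.072² + 0.161²) = −0.08 to 0.10 + √(0.201² + 0²) = 0.30.

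**The case against.** - **The obvious examples are not assigned to this model.** A reader might infer that safety comparisons would go unreported when the model fails. The article does not support that. Data analysis says adverse effects and antibiotic use will be described, and abnormal blood results go to the data monitoring committee. Neither depends on a model converging. This objection stands in full.
- **No named outcome is tied to logistic regression.** The two-point threshold on the Global Ratings of Change is a natural candidate, but the article does not say it will be dichotomised for modelling. This stands as a limit on reach. The article does, however, plan logistic regression for whatever binary measures there are.
- **The wording could cover exact or penalised versions, and the analysis plan may settle the estimator.** This is partly right: the covariate list and the choice of software routine do belong there. But the article already fixes the method class and requires confounder control throughout, while giving an alternative for continuous outcomes only. The point concerns how that stated choice performs at this size.
- **A 20 v 20 fit is the least favourable set-up.** This is fair. The article contrasts individualised, standardised and placebo treatment, which may mean 20/20/40. The pooled figures are therefore given alongside.
- **The trial is exploratory, and its Discussion ties the later power calculation to the variance of continuous outcomes.** This is true and lowers the weight. A reader might infer that a definitive trial would be sized on exaggerated odds ratios. The documents do not say so.

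**Conclusion.** The point holds as a minor one about choice of method. Non-finite estimates are frequent only at event rates of about 10% or less, and the problem has largely gone by 15–20%. For common outcomes the overstatement ranges from about 5% (placebo pooled, no covariates) to 24–29% (20 v 20, four covariates), and it is always smaller than the sampling error. It arises only where there is a true effect; with no effect, the estimate has no systematic direction.

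The sizes depend on assumed event rates, covariate numbers and covariate effects, and on whether placebo groups are pooled. Dropout would make them somewhat worse. Only secondary, exploratory binary measures are touched. The count-based primary outcomes and the descriptive safety and antibiotic data are not.

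**What to change.** Replace the clause on binary measures with wording to this effect: for each binary measure compared between groups, report the counts, the percentages and the risk difference with a Newcombe or exact 95% interval; where adjustment is wanted, use Firth penalised logistic regression with at most two covariates fixed in advance.

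The cost is one sentence and slightly different software commands. Fewer covariates can be adjusted for, so the general promise to control for confounders needs a matching limit for binary measures. The change does not add information: estimates for rare events stay very imprecise. If no event occurs in either group, only the descriptive counts and the interval for the risk difference can be reported.
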